#### Randomization and blinding

2.3.1

After completing the diagnostic interview and the baseline assessment, randomization will be performed in a 1:1 ratio by an independent researcher who is not involved in the project using a computer-based algorithm provided by the software *SoSci Survey* (Leiner, 2021). The diagnostic interviews will thus be conducted blindly; that is, the clinical interviewers do not know what treatment a participant will be allocated to in case of inclusion (*allocation sequence concealment*; Altman and Schulz, 2001). During the clinical interviews, participants are told that the assigned waiting time varies randomly between 0 and 12 weeks to prevent frustration, dropout, or other biases in the control group. Following randomization, all participants receive an email with either a code to immediately access the intervention or information that they will receive a code in 12 weeks. Finally, the group allocation variable will be blinded to allow unbiased data analyses. For this purpose, an independent researcher will delete all information in the data set indicating the group membership.

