#### Primary and secondary outcome analyses

2.5.1

To statistically evaluate the effectiveness of the web-based intervention for patients with BED compared to the waitlist control condition, growth models within a multilevel modeling (MLM) framework will be conducted. MLMs are regression-based models that allow considering the nested data structure, i.e., the three repeated assessments (level 1) nested within patients (level 2), define change as a continuous process, and have more power when handling missing data than traditional approaches (Hesser, 2015; Kahn and Schneider, 2013; Tasca and Gallop, 2009). To test whether there is a treatment × time interaction effect, we will set up MLMs of increasing complexity (Kahn and Schneider, 2013). The first model will have only random intercepts on the person-level (level 1), and no predictors will be included. In the second model, the fixed effects of time (study entrance, 6 weeks, 12 weeks) and treatment (intervention versus control group) will be added. In a final model, we will examine if the change in symptom severity differs between the intervention and control group by adding the treatment × time interaction. Model fit of the competing models will be compared employing likelihood ratio tests for nested models and the Akaike Information Criterion. A significant treatment × time-interaction with a more substantial change in participants undergoing the 12 weeks of treatment compared to the waitlist group will indicate confirmation of the hypotheses (Raudenbush and Bryk, 2002). The magnitude of treatment effects will be estimated as Cohen's *d* effect size (Feingold, 2013).

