### Statistical power and sample size

2.6

To determine the required sample size, we conducted power calculations using the R package *powerlmm* (Magnusson, 2018). Based on previous meta-analytic evidence for the effectiveness of web-based interventions for BED (Beintner et al., 2014; Haderlein, 2022; Hilbert et al., 2019), we chose medium effect sizes of Cohen's *d* = 0.50 as a benchmark for expected pre-post differences between the intervention group and the waitlist control group. Power calculations using an intraclass correlation of .40 (Arend and Schäfer, 2019), a power of .80, and an alpha level of .05 resulted in a required sample of *N* = 152. Additional power analyses, including possible dropouts of 20% and different intra-class correlation coefficients, can be found in the supplementary material (Fig. S3), strengthening our conclusion that our sample will be sufficiently large to detect a medium effect under different statistical assumptions.

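### The primary model leaves the baseline group difference free, so its test is in effect a change-score comparison; fixing a common baseline mean would raise power at N = 152 from .80 to about .92 at the planning ICC of .40

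*Protocol article*

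**What the plan says.** Section 2.5.1 plans multilevel growth models with three repeated assessments per patient, baseline included. Treatment and time enter together: "In the second model, the fixed effects of time (study entrance, 6 weeks, 12 weeks) and treatment (intervention versus control group) will be added". The final model tests whether change differs between arms "by adding the treatment × time interaction". A significant interaction in the expected direction confirms the hypothesis. No baseline covariate and no constraint on the baseline means is stated for this model. Growth models are described as methods that "define change as a continuous process, and have more power when handling missing data than traditional approaches", which suggests linear time, but no coding is given; the R script (Supplement S2) is not shown.

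Section 2.3.1 fixes the order of events: "After completing the diagnostic interview and the baseline assessment, randomization will be performed in a 1:1 ratio".

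Section 2.6 gives the planning figures: "we chose medium effect sizes of Cohen's *d* = 0.50 as a benchmark for expected pre-post differences"; "Power calculations using an intraclass correlation of .40"; "a power of .80, and an alpha level of .05". The result is N = 152. Dropout of 20% appears only in supplementary power analyses.

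**The concern.** Once the interaction is in the model, the treatment main effect is the difference between arms at baseline. Randomisation comes after the baseline assessment, so this difference is zero in expectation. Estimating it freely spends information on a quantity known by design and forces the treatment effect to be measured as change from each arm's own observed baseline. When the correlation between visits is modest, subtracting the whole baseline value adds noise.

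What is at stake is power. The protocol expects notable dropout (sections 2.5.2 and 3.1), N = 152 carries no allowance for it, and the baseline binge count is already collected from everyone.

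**Working it through.** **Inputs.** From section 2.6: d = 0.50, ICC ρ = .40, power .80, alpha .05, N = 152 (76 per arm). From section 2.5.1: visits at 0, 6 and 12 weeks and a random intercept. Assumed: a two-sided test, d in units of the total SD, and equal variances at each visit. Under a random intercept the ICC is then the correlation between any two visits. Write v for the variance of the estimated week-12 effect multiplied by n/2 (n per arm, total SD = 1).

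**Step 1. Reproduce the plan's figure (free baseline).** The variance of a change score is v = 2(1 − ρ) = 2 × 0.60 = 1.20. Then n = 2 × (1.960 + 0.842)² × v / d² = 2 × 7.849 × 1.20 / 0.25 = 75.3, so 76 per arm and N = 152, exactly as stated. Generalised least squares gives the same 1.20 with linear or categorical time. Noncentral t power at 76 per arm is .798.

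**Step 2. Constrain the arms to a common baseline mean, complete data.**
- Categorical time, week-12 contrast: v = 1 − ρ² = 1 − 0.16 = 0.84. Baseline now enters with coefficient ρ = .40 instead of 1. Then n = 2 × 7.849 × 0.84 / 0.25 = 52.7, so 53 per arm and N = 106.
- Linear time t = (0, 0.5, 1): the inverse covariance matrix is (1/0.6)(I − 0.2222 J), where J is the all-ones matrix. With one intercept shared by the arms, v = 1 / (t′V⁻¹t) = 1 / [(1.25 − 0.2222 × 2.25) / 0.6] = 1 / 1.25 = 0.80. Then n = 50.2, so 51 per arm and N = 102.

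**Step 3. Power at N = 152.** The noncentrality is 0.5 × √(76 / 2v), with 150 degrees of freedom.

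| Model | v | Noncentrality | Power |
|---|---|---|---|
| Free baseline (planned) | 1.20 | 2.81 | .798 |
| Common baseline, categorical time | 0.84 | 3.36 | .916 |
| Common baseline, linear time | 0.80 | 3.45 | .928 |

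**Step 4. With 20% dropout.** The timing is not given. Assume half leave before week 6 and half after, unrelated to outcome. Then v is 1.40 for the planned model (power about .735), 1.04 for the constrained categorical model (.85) and 0.97 for the constrained linear model (.87). Putting all dropout before or all after week 6 moves these powers by about .01.

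**Step 5. Other correlations.** For complete data and categorical time the variance ratio is 2(1 − ρ)/(1 − ρ²) = 2/(1 + ρ).

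| ρ | Ratio | Power, planned | Power, constrained |
|---|---|---|---|
| .30 | 1.54 | .735 | .894 |
| .40 | 1.43 | .798 | .916 |
| .50 | 1.33 | .865 | .943 |
| .60 | 1.25 | .928 | .969 |
| .70 | 1.18 | .977 | .990 |
| .84 | 1.09 | about 1 | about 1 |

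The last row uses the test-retest reliability quoted for the binge count in section 2.4.4. It serves as an upper end for the correlation over 12 weeks, not as a planning value.

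**The case against.** The strongest reply is that nothing in the plan is wrong. A treatment × time mixed model is unbiased under randomisation, and N = 152 was sized for exactly this model. That stands. Four stronger readings might be inferred, and the documents support none of them.

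- **That the trial is undersized, or needs 43% more patients than it should.** The ratio 152/106 = 1.43 holds only for a correlation of .40, complete data and a categorical week-12 contrast. It is 1.50 under linear time, about 1.35 with the dropout assumed in Step 4 (1.40/1.04) and 1.09 at a correlation of .84. The plan reaches its stated power before dropout.
- **That the model throws baseline away.** It uses baseline, with too large a coefficient. Analysing week 12 alone (v = 1) would need 2 × 7.849 × 1 / 0.25 = 62.8, so 63 per arm and N = 126. This is fewer than 152, because below a correlation of .5 subtracting baseline is worse than ignoring it.
- **That chance imbalance in binge frequency goes uncorrected.** The change score already removes it, and over-corrects. The baseline tests in section 2.5.3 are a separate robustness step.
- **That linear time distorts the week-12 effect for early leavers.** This concerns time coding, not the baseline constraint. The coding is only inferred, and any distortion needs an assumed plateau and dropout pattern.

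It also stands that the practical gain is small if the true correlation is .70 or more, and that equal variances at each visit are an approximation for an episode count.

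**Conclusion.** The point holds as a loss of efficiency in a valid analysis. The stated model estimates a baseline difference that the design sets to zero, and its test of the baseline-to-week-12 effect is in complete data a change-score comparison; the exact reproduction of N = 152 from the change-score variance supports this reading. At the planning ICC the constraint cuts the variance by 30% (0.84/1.20) or by a third (0.80/1.20). Equivalently, 102 to 106 patients with complete data would give the power for which 152 are planned. With 20% dropout the constrained model stays above the planned power, whereas the planned model falls below it. The constrained variance is smaller at every correlation tried.

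The sizes rest on the assumptions listed in the working and on reading the model from the article text, since the R script might specify it differently.

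**What to change.** Before unblinding, specify in section 2.5.1 and in the R script a baseline-constrained longitudinal model: one common baseline mean, time as three categories, and treatment × week 6 and treatment × week 12 terms, with the week-12 contrast as the primary test. Equivalently, model the week-6 and week-12 outcomes with baseline binge count × time as covariate. Use the same form for the secondary outcomes measured at these visits.

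The cost is a changed formula and a dated, justified amendment, because the primary model is already published and recruitment is under way. The planned blinding of the allocation variable (section 2.3.1) allows the change to be fixed without knowledge of results. It needs no further patients or data and introduces no bias under randomisation.

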### Objectives and hypotheses

2.1

The overarching goal of our trial is to evaluate the 12-week web-based self-help intervention *Selfapy* for BED, which employs CBT methods targeting binge eating pathology directly (Munsch, 2003; Munsch, 2007), as well as processes associated with the maintenance of BED, such as emotion regulation, stress management, and self-esteem (Dingemans et al., 2017, Linardon et al., 2019; Sipos and Schweiger, 2016). The intervention can be used via desktop browsers and mobile devices and has been established alongside a program targeting the treatment of bulimia nervosa in routine care settings (for details, see Hartmann et al., 2022).

Based on the effectiveness of online interventions for BED (Beintner et al., 2014; Haderlein, 2022), we expect that the program will lead to a greater reduction in the frequency of binge eating episodes over the twelve weeks of treatment compared to a waitlist control condition. Moreover, we assume that there will be a higher decline in global eating disorder symptoms and functional impairments as well as a higher increase in well-being and work capacity in the intervention group compared to the waitlist control group (Ágh et al., 2015, Jenkins et al., 2021, Safi et al., 2022). Finally, we expect that the web-based intervention for BED will be associated with a significantly higher reduction in comorbid psychopathology, increased self-esteem, and an improved ability to regulate negative emotions after treatment (Dingemans et al., 2017, Linardon et al., 2019, Prefit et al., 2019).

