#### Secondary confirmatory outcomes

2.4.5

•Changes in global eating psychopathology: Global eating psychopathology will be investigated as a secondary outcome using the total score of the EDE-Q (Hilbert et al., 2007), which is derived from the dimensions of *weight concern*, *shape concern*, *eating concern*, and *restraint*. The eating psychopathology dimensions are assessed with 22 items on a 7-point Likert scale and Cronbach's α ranges between .85 and .93 for the subscales and .97 for the total score (Hilbert et al., 2007).•Changes in the weekly frequency of binge eating episodes, overeating, and regular eating: The *Weekly Binges Questionnaire* (WBQ; Munsch et al., 2007; Munsch et al., 2019) will be used as a continuous method to monitor the frequency of objective and subjective binge eating episodes and overeating as secondary outcomes of BED symptom alterations. Weekly text messages throughout the study period will remind participants to report the occurrence and rate the severity of each of these eating episodes as well as regular eating within the last week on an 11-point scale (Munsch et al., 2007; Munsch et al., 2019).•Changes in eating-disorder-related clinical impairments: To assess hypothesized reductions in clinical impairments specific to eating disorders, we will employ the *Clinical Impairment Assessment* scale (CIA; Bohn et al., 2008), which measures overall and domain-specific impairments (i.e., cognitive, social, and personal). The CIA consists of 16 items rated on a 7-point Likert scale and demonstrates excellent internal consistency (Cronbach's α = .97), construct validity, and sensitivity to change (Bohn et al., 2008).•Changes in well-being: To measure assumed increases in well-being, we will use the frequently employed *World Health Organization-Five Well-Being Index* (WHO-5; Bech et al., 2003). The WHO-5 assesses general well-being based on five items, rated on a 6-point scale, and has high internal consistency (Cronbach's α = .92; Brähler et al., 2007).•Changes in work capacity: To address the increasing significance of health economic evaluations (Jenkins et al., 2021; Safi et al., 2022), changes in work capacity and productivity will be measured based on the *iMTA Productivity Cost Questionnaire* (iPCQ; Bouwmans et al., 2015). The iPCQ examines absences from work and productivity losses due to sickness-related restrictions in work efficiency. Test-retest reliability of the iPCQ is excellent concerning the reported number of sick leave days (ICC = .83) and moderate regarding the number of days at work while impeded (ICC = .56) and efficiency rates (ICC = .73; Bouwmans et al., 2013).

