### Statistical methods

2.5

The analysis strategy for this trial consists of four steps: (1) descriptive analyses, (2) confirmatory analyses of the primary outcome, including sensitivity analyses, (3) analyses of secondary outcomes, including sensitivity analyses, (4) moderator and mediator analyses as well as analyses of the naturalistic EMA measures. All statistical tests will be conducted using R Statistics (R Core Team, 2020); see the R script in the supplementary materials (Supplement S2).

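### One confirmation rule covers the primary and five secondary instruments labelled confirmatory, with no order or adjustment stated, so a false secondary confirmation has a chance of about 9–18%, against 2.5% for a single test

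*Protocol article*

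**What the plan says.** Three places in the protocol article bear on this.

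- **The labels.** Section 2.4.5 is headed "Secondary confirmatory outcomes" and lists EDE-Q total, WBQ, CIA, WHO-5 and iPCQ. Table 2 groups the same five instruments in the same way.
- **The analysis steps.** Section 2.5 numbers them differently: "2) confirmatory analyses of the primary outcome, including sensitivity analyses, (3) analyses of secondary outcomes, including sensitivity analyses". Only the primary analysis is called confirmatory there.
- **The decision rule.** Section 2.5.1, whose heading names both primary and secondary outcomes, gives a single rule: a significant treatment × time interaction "with a more substantial change in participants undergoing the 12 weeks of treatment compared to the waitlist group will indicate confirmation of the hypotheses". The hypotheses are those of section 2.1. They cover binge frequency and also global symptoms, impairment, well-being and work capacity.

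The only significance level in the article is in section 2.6, where "a power of .80, and an alpha level of .05 resulted in a required sample of" 152. It is attached to the sample size. Sidedness is not given.

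**The concern.** The rule and the labels together give each secondary outcome its own route to a confirmed hypothesis. Nothing in the article makes that route depend on the primary result, puts the secondaries in order, or divides the error among them. A trial with no effect on binge eating could therefore still report that improved work capacity or well-being was confirmed. These outcomes carry weight of their own: section 2.4.5 links work capacity to health economic evaluation, and section 3.1 lists the secondary outcomes among the trial's strengths.

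Sections 2.4.5 and 2.5 also disagree on which outcomes are confirmatory. A reader of the final report could not tell from the article which claims were meant to be tested with controlled error.

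**Working it through.** **1. Sidedness, from the plan's own sample size.** Section 2.6 takes d = 0.50 "as a benchmark for expected pre-post differences between the intervention group and the waitlist control group", with ICC .40, power .80 and alpha .05. Section 2.3.1 gives 1:1 allocation, and section 2.5.1 gives three assessments.

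For a random-intercept growth model with total variance 1, the residual variance is 1 − .40 = .60. With times scaled to 0, 0.5 and 1, the sum of squared deviations is 0.5. The SD of a person's slope over the full period is √(.60/.50) = 1.095.

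- Two-sided: n per arm = 2 × (1.960 + 0.842)² × 1.2 / 0.25 = 75.4, rounded up to 76. N = 152, as stated.
- One-sided: n per arm = 2 × (1.645 + 0.842)² × 1.2 / 0.25 = 59.4, rounded up to 60. N = 120, which does not match.

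Two-sided testing at .05 is therefore the reading that fits the article, although it is inferred.

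**2. Error per test under the stated rule.** Confirmation needs significance and a larger change in the intervention arm. Under the null, a two-sided .05 test meets both conditions with probability .05 / 2 = .025.

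**3. Number of tests.** Five instruments carry the confirmatory label, so one test each gives k = 5. WBQ covers objective binges, subjective binges, overeating and regular eating, and iPCQ covers absence and productivity loss. Up to about eight tests is thus a plausible reading, but the article does not state a count.

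**4. Chance of at least one false confirmation among the secondaries, all nulls true.** If the tests are independent, this is 1 − (1 − .025)^k:

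- k = 5: 1 − .975⁵ = 11.9%
- k = 8: 1 − .975⁸ = 18.3%

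The article gives no correlation among the outcomes. A simulation of equally correlated normal test statistics (1,000,000 draws) gives the effect of assumed values:

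| Tests | Correlation 0 | .5 | .7 |
|---|---|---|---|
| 5, favourable direction only | 11.9% | 9.1% | 7.4% |
| 8, favourable direction only | 18.4% | 12.4% | 9.6% |
| 5, either direction | 22.6% | 18.3% | 14.8% |
| 8, either direction | 33.7% | 24.9% | 19.1% |

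The favourable-direction rows match the article's rule. The 18.4% is the simulated counterpart of the exact 18.3%.

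**5. Cost of controlling the error.** Holm over five endpoints starts at .05 / 5 = .01. With 76 per arm, d = 0.5 and SD 1.095, the expected test statistic is 0.5 / √(2 × 1.2 / 76) = 2.81. Power is Φ(2.81 − 1.96) = 80% at .05 and Φ(2.81 − 2.58) = 59% at .01.

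**The case against.** **Condensed article.** Handling of multiple secondary endpoints is often left to an analysis plan, and the R script in Supplement S2 is not shown. This stands as a limit: the point can only be that no control is stated in the article. It does not remove the point, because the article itself fixes the labels and the confirmation rule, and these conflict with its own analysis steps.

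**The primary is protected.** There is one primary outcome, analysed in its own step. This stands in full: the secondaries do not inflate its type I error.

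**The count may be smaller.** Section 2.1 names four secondary hypotheses at this level. Section 2.5.3 places the weekly binge data among the additional analyses, although section 2.4.5 and Table 2 call WBQ confirmatory. With four tests the chance is 1 − .975⁴ = 9.6% if independent. That is smaller, but still well above 2.5%.

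**Two stronger readings are tempting and are not supported.**

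- A reader might put the chance of false confirmation at 18–34%. That range counts significant results in either direction. The rule requires more change in the intervention arm, so a result favouring the waitlist confirms nothing.
- A reader might see a contradiction in section 2.1 expecting that the intervention "will be associated with a significantly higher reduction in comorbid psychopathology, increased self-esteem, and an improved ability to regulate negative emotions", since section 2.4.6 calls those measures exploratory. A directional expectation can be stated for an exploratory outcome, so this is not in itself an error.

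**Conclusion.** The point holds, limited to secondary claims. The article labels five secondary instruments confirmatory, applies one confirmation rule to them and to the primary, and states no order, gate or adjustment. Section 2.5 meanwhile calls only the primary analysis confirmatory.

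If every null is true, the chance of at least one false secondary confirmation is about 9–12% with five tests and about 12–18% with eight. This assumes two-sided .05 tests and correlations between .5 and 0. At a correlation of .7 the figures are 7.4% and 9.6%, so the error stays above both 2.5% and 5% in these scenarios. Eight tests, the correlations and the use of .05 for each secondary are assumptions. The article does not show that error control is absent from every trial document, and the validity of the primary test is not in doubt.

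**What to change.** State in section 2.5.1 that only the primary test confirms effectiveness, and use the same labels in sections 2.4.5 and 2.5 and in Table 2. Then choose one of two options and record the choice before the group allocation is unblinded for analysis.

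1. **Drop the confirmatory label for the secondaries** and report them as estimates with confidence intervals, without confirmation wording. This takes a few sentences and costs no power, but gives up confirmatory secondary claims.
2. **Keep confirmatory secondary claims.** Name one endpoint per instrument (five in all) and test them with Holm at family-wise .05, only if the primary is significant. Report all other outcomes as estimates with intervals. Power for a d = 0.5 secondary falls from about 80% to about 59% at the strictest Holm step. That figure assumes the ICC of .40 and no dropout, and it comes before the further requirement that the primary succeed.

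Under either option the power of the primary test is unchanged.
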